## Abstract

**Background:**

Spinal metastases of lung cancer (SMLC) usually have a high degree of malignancy and require multimodality treatment. Patients with SMLC who experience clinical symptoms (eg, local pain, emerging or potential spinal instability, and progressive neurological dysfunction) require surgical treatment. However, there are discrepancies in the comparison of outcomes between surgical treatment and nonsurgical treatment.

**Objective:**

This paper presents the protocol for a study that aims to compare the clinical outcomes of surgical treatment and nonsurgical treatment for SMLC, explore the prognostic factors of SMLC, and establish a survival prediction model based on these prognostic factors.

**Methods:**

This is a prospective cohort study, with an anticipated sample size of 240 patients (120 patients in the surgical group and 120 patients in the nonsurgical group). We will collect baseline data, including demographic, clinical, and radiological information, as well as data from patient-reported questionnaires. Patients will be followed up at 3, 6, 12, and 24 months after treatment, and survival status will be assessed every 3 months. The primary outcome is the overall survival period. Prognostic factors associated with overall survival will be analyzed by univariate and multivariate Cox proportional hazards regression. Odds ratios with 95% CIs will be presented. Statistical significance is set at *P*<.05.

**Results:**

This study has been approved by our institute’s Medical Science Research Ethics Committee (IRB00006761-M2021085) after a careful audit of the design and content. Patient enrollment began in June 2022 at our hospital. Data collection is expected to be completed by early 2026, and the study results will be published by mid-2027.

**Conclusions:**

In this study, we propose to set up a prospective cohort of patients with SMLC to investigate the outcomes between surgical treatment and nonsurgical treatment. We will explore the role of surgical treatment in SMLC and provide guidance to peer surgeons.

**Trial Registration:**

Chinese Clinical Trial Registry, ChiCTR2100048151; http://www.chictr.org.cn/showproj.aspx?proj=129450

**International Registered Report Identifier (IRRID):**

DERR1-10.2196/38273

## Introduction

### Background

The effective integration of therapeutic modalities into the treatment of metastatic lung cancer on the spine is a source of debate. Lung cancer is a moderate to high malignancy, and metastasis to the spine usually represents the end stage of the disease [1,2]. According to the scoring systems for spinal metastasis by Tomita et al [3] and Tokuhashi et al [4], patients with spinal metastases of lung cancer (SMLC) are expected to live less than 1 year. Thus, more conservative treatments have been given in the past. In recent years, advances in radiation therapy and systemic antitumor drugs, such as stereotactic body radiotherapy (SBRT), target therapies, and immunological therapies have demonstrated encouraging therapeutic outcomes and have largely expanded the survival time of patients with SMLC [5-11]. At the same time, surgical treatment has been widely accepted for some SMLC cases [12]. A comprehensive treatment, composed of antitumor drugs, radiotherapy, and surgery, has been the current state-of-the-art therapeutic modality for SMLC.

Generally, patients with SMLC experiencing the following symptoms are referred for surgery: severe and refractory local pain, emerging or potential spinal instability, and progressive neurological dysfunction [8,13-17]. After the surgery, adjuvant therapies, including radiotherapy and systemic drugs, are undertaken. Most researchers have stated that adjuvant radiotherapy should be completed around 6 weeks after the operation to spare time for physical recovery and avoid problems related to wound healing [18]; yet, this is difficult to do in a real-world setting [19]. Additionally, previous studies have described discrepancies in the efficacy of surgical treatment for patients with SMLC [20]. According to these works, the median survival time after surgery was reported to range from 2 to 14 months [21]. Because of limitations that included a retrospective study design, no control group, etc, the conclusions of related studies lack high-quality evidence.

### Objective

In our study, a prospective, specific disease cohort of SMLC will be used to compare the effectiveness of surgical treatment and nonsurgical treatment. This study will provide useful information to explore the role of surgical treatment in comprehensive SMLC treatment and develop suitable treatment guidelines.

The primary aim of this study is to investigate and compare treatment outcomes in patients with SMLC. In addition, we also plan to analyze various prognostic factors of SMLC, such as treatment modalities, tumor subtypes, pre- and postoperative neurological function, and more.

## Methods

### Study Design

This study is a prospective cohort study. We will compare the treatment outcomes of surgical and nonsurgical methods for SMLC in a real-world clinical scenario. The study will enroll 240 patients (120 patients in the surgical group and 120 patients in the nonsurgical group) from June 1, 2022, to June 30, 2027. The patients will be visited postoperatively at 3, 6, 12, and 24 months. The study is due to be completed on June 30, 2029.

### Sample Size and Study Timeline

In this study, we plan to compare the overall survival (OS) time between the two groups and explore its prognostic factors. The sample size calculation was based on the survival time and estimation of influencing factors. According to an unpublished retrospective study performed at our center and previous literature [20,21], the average OS time was 11 (SD 4) months in the surgical group and 9 (SD 3) months in the nonsurgical group. Assuming an overall Type 1 error (α) of .05 and Type II error (β) of .1, we need 66 patients in each group. Additionally, there are 12 predictive factors we plan to analyze in the prediction model. According to the sample size estimation method for multivariable regression models, 100 cases in each group are needed (the ratio of surgical to nonsurgical group is 1:1). Considering a final follow-up rate of 80%, a minimum of 120 patients will be required for each group. There were approximately 25 patients undergoing surgery per year at our center; therefore, we plan to enroll the patients over the next 5 years. Since more patients are treated nonsurgically than surgically, all nonsurgical patients treated during the first 5 years will be enrolled.

The study duration is estimated to be 7 years to ensure that all recruited patients are followed up for 2 years. Each visit’s timeline and tasks are presented in Multimedia Appendix 1.

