## Results

Study design, ethical review, and research registration have been completed. Enrollment commenced in June 2022, and enrolled patients are being visited regularly. Patient enrollment is expected to be completed by June 2027, and the study results will be submitted for publication in early 2029.

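### The enrolment target of 120 per group is inflated wrongly for 80% follow-up: it leaves 96 evaluable against the required 100 (125 is needed), surgical accrual leaves almost no margin for the correction, and the study dates conflict.

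*Protocol article*

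**What the plan says.** All of the following is in the protocol article.

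- **Requirement.** The section Sample Size and Study Timeline gives 66 per group for the survival comparison. For the prediction model with 12 factors it gives a larger number: "100 cases in each group are needed (the ratio of surgical to nonsurgical group is 1:1".
- **Allowance for loss.** The same section continues: "Considering a final follow-up rate of 80%, a minimum of 120 patients will be required for each group". The resulting total of 240 is repeated in the Abstract and in Study Design.
- **Accrual.** "There were approximately 25 patients undergoing surgery per year at our center", and enrolment is planned over five years. The section adds that nonsurgical patients are more numerous and that all of them treated in those five years will be taken in.
- **Dates.** Study Design enrols "120 patients in the nonsurgical group) from June 1, 2022, to June 30, 2027" and then says: "The study is due to be completed on June 30, 2029". The sample size section gives a seven-year duration so that each patient has two years of follow-up. The Abstract says: "Data collection is expected to be completed by early 2026, and the study results will be published by mid-2027". The Results section keeps June 2027 as the end of enrolment but says that "the study results will be submitted for publication in early 2029".

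**The concern.** The planned enrolment does not deliver the number that the same paragraph calls necessary, under the loss rate that the paragraph itself assumes. The larger of the two sample size requirements drives the headline target, so the slip carries into the 240 patients quoted throughout. At stake is the support for the survival prediction model, which is a stated objective.

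Two further matters bear on whether the target can be met and when the data are complete. The surgical group has a finite supply, and the corrected target falls almost exactly on it. The article also gives dates that cannot all be true, so a reader cannot tell when data collection in this time-to-event study ends.

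**Working it through.** **1. The comparison figure of 66 reproduces.** Inputs from the sample size section: means 11 and 9 months, SDs 4 and 3, α = 0.05, β = 0.1. With the usual normal formula, two-sided:

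n = (1.960 + 1.282)² × (4² + 3²) / (11 − 9)² = 10.51 × 25 / 4 = 65.7, so 66 per group.

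**2. The enrolment figure of 120 does not.** Inputs: 100 required per group, 80% final follow-up.

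- Correct inflation: 100 / 0.80 = 125 per group, 250 in total.
- The stated figure comes out only as 100 × (1 + 0.20) = 120.
- Yield of the stated figure: 120 × 0.80 = 96 per group, 4 short.
- Follow-up at which 120 would suffice: 100 / 120 = 83.3%, not 80%.

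**3. Effect on the survival comparison.** Inflated correctly, 66 / 0.80 = 82.5, so 83 per group, well under 120. With 96 evaluable per group, power by the plan's own means formula is about 97% two-sided. The deficit concerns only the prediction model: 192 / 12 = 16.0 patients per factor instead of 200 / 12 = 16.7, if both groups stop at 120.

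**4. Surgical supply.** At 25 per year, five years give 125. The window in Study Design, June 1, 2022 to June 30, 2027, is about 5.08 years and gives about 127.

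- Share needed for 120: 120/127 to 120/125 = 94% to 96%.
- Share needed for 125: 125/127 to 125/125 = 98% to 100%.

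The protocol gives no enrolment share, so the following is an assumed range:

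| Share of operated patients enrolled | Enrolled | Evaluable at 80% |
|---|---|---|
| 100% | 125–127 | 100–102 |
| 95% | 119–121 | 95–96 |
| 90% | 112–114 | 90–91 |
| 80% | 100–102 | 80–81 |

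**5. Dates.** Last enrolment on June 30, 2027 plus 24 months is June 30, 2029, so Study Design and the seven-year duration agree.

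- The Abstract's early 2026 (taken as January 1 to March 31) is 3.59 to 3.83 years after the start. At 25 per year that is about 90 to 96 surgical patients, of whom 25 × 1.59 to 25 × 1.83, about 40 to 46, were enrolled at least two years before. Neither 120 nor 125 is reachable by then.
- The Abstract's publication in mid-2027 coincides with the close of enrolment and precedes completion by about two years.
- The Results section's submission in early 2029 precedes the completion date by some three to six months.

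**The case against.** **The gap is small and not sharp.** It is 4%. How 100 was obtained from 12 factors is not shown, so it should not be read as a cliff edge. Patients lost to follow-up still contribute time until censoring in the Kaplan-Meier, log-rank and Cox analyses. All of this stands, and it limits the consequence. It does not rescue the arithmetic, because the protocol itself sets 100 as needed and itself discounts enrolment by the follow-up rate.

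**The target is worded as a minimum, and nonsurgical patients are plentiful.** This also stands. If every eligible nonsurgical patient over five years is enrolled, that group may exceed 120. Study Design fixes 120 for it, so the text is not wholly consistent. A shortfall of 8 out of 200 therefore holds only if both groups stop at 120.

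**Can accrual make up the gap?** A reader might infer that the stated rate and dates rule out the corrected target. The documents do not support that: the Methods window nominally yields 125 to 127 operated patients against 125 needed. What remains is the lack of slack, since Patient Enrollment and Group Allocation requires consent and sets exclusion criteria. Only the Abstract's early-2026 date would make the target unreachable.

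**Does early 2029 mean an immature analysis?** At 25 per year, the 6 to 12 surgical patients enrolled in the last three to six months would not have reached 24 months by then, and a reader might count them all as incomplete. That overstates the matter. Follow-up ends at death, and the plan assumes mean survival of 11 and 9 months, so on its own figures most would already have had the primary event. The passage also gives an expected submission date, not a data cut-off.

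**Conclusion.** The concern holds as an arithmetic error in the enrolment target. Under the protocol's own inputs of 100 required and 80% retained, the figure is 125 per group, and 120 yields 96. The deficit is 4 per group, certain for the surgical group if it stops at 120, and contingent for the nonsurgical group. It affects the prediction model's stated requirement and not the survival comparison, which needs 66 per group by the plan's calculation.

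Surgical accrual is tight but not impossible: the corrected target needs 98% to 100% of operated patients, on the stated rate of about 25 per year.

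The date conflict is a separate matter. The Abstract's two dates contradict enrolment to June 2027 and completion on June 30, 2029, and the early-2029 submission falls before that completion. The documents do not show that the analysis would be run on a truncated cohort; they show that the dates must be reconciled.

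The derivation of 100 from 12 factors could not be checked and is taken as stated.

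**What to change.** 1. In Sample Size and Study Timeline, restate the target in one of two ways, and carry it through the Abstract and Study Design:
   - 125 per group (250 in total); or
   - 120 per group with 96 expected evaluable, noting that 100 would be reached only if follow-up is at least 83.3%.
2. State that about 25 operations a year over the enrolment window supply about 125 to 127 surgical patients before exclusions and refusals, so there is almost no margin in that group.
3. Name one data cut-off consistent with Study Design and the seven-year duration, June 30, 2029, and align the early-2026, mid-2027 and early-2029 dates to it.

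These are text corrections. The cost is a slightly less favourable stated number, either a higher target with no slack in the surgical group or an admitted 96 evaluable, and a later publication date.

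### The allowance for 80% follow-up is miscalculated: 120 per group leaves 96 with complete follow-up, not the 100 the plan says it needs

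*Protocol article*

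**What the plan says.** The Sample Size and Study Timeline section of the Protocol article gives two requirements and one allowance.

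- **Survival comparison.** 66 patients per group, from the assumption that "the average OS time was 11 (SD 4) months in the surgical group and 9 (SD 3) months in the nonsurgical group", with a type I error of .05 and a type II error of .1.
- **Prediction model.** The plan says that "there are 12 predictive factors we plan to analyze in the prediction model", and continues: "According to the sample size estimation method for multivariable regression models, 100 cases in each group are needed". The ratio is fixed: "the ratio of surgical to nonsurgical group is 1:1".
- **Loss to follow-up.** "Considering a final follow-up rate of 80%, a minimum of 120 patients will be required for each group".

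The resulting total is repeated elsewhere. The Abstract (Methods) gives an enrolment of 240, split 120 and 120, and the Study Design section gives the same figures.

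**The concern.** Of the two requirements, 100 per group is the larger, so it determines the size of the study. If only 80% of patients are followed to the end, the number enrolled must be the number needed divided by 0.80. The printed 120 is too small for that, and it matches the common slip of adding the loss percentage to the number needed.

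What is at stake is whether the headline sample size supports its own derivation. The plan calls 120 a minimum, so a reader will take it as the floor that secures 100 per group. Under the plan's own follow-up assumption it does not. The requirement that is missed belongs to the survival prediction model, which is one of the stated objectives.

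**Working it through.** **Inputs** (all from Sample Size and Study Timeline, Protocol article)

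- Needed per group for the prediction model: 100
- Needed per group for the survival comparison: 66
- Final follow-up rate: 0.80, so loss d = 0.20
- Planned enrolment: 120 per group, 240 in total
- Surgical accrual: about 25 a year over 5 years

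**Step 1. Does the 66 reproduce?** With a difference of 2 months, variances 4² = 16 and 3² = 9, two-sided α = .05 and 90% power:

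n = (1.96 + 1.2816)² × (16 + 9) / 2² = 10.508 × 6.25 = 65.7, so 66 per group.

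It does. The article does not state sidedness in this section, but the two-sided calculation gives the printed figure (one-sided gives 54). The step before the follow-up allowance is therefore sound for this requirement. The 100 cannot be checked, because the article does not show how it was derived; it is taken as stated.

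**Step 2. Can the 120 be reproduced?** The correct inflation is n / (1 − d). The usual mistake is n × (1 + d).

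| Starting requirement | n / 0.80 | n × 1.20 |
|---|---|---|
| 66 | 82.5, so 83 | 79.2, so 80 |
| 100 | 125 | **120** |

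Only 100 × 1.20 returns the printed 120. Rounding is not an explanation, because 125 is already a whole number.

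**Step 3. What does 120 yield?**

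- Per group: 120 × 0.80 = 96, against 100 needed (4 short)
- In total: 240 × 0.80 = 192, against 200 needed (8 short, 8/200 = 4%)
- Patients per predictive factor: 192/12 = 16.0, against 200/12 = 16.7

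**Step 4. What follow-up would make 120 sufficient?** 100/120 = 83.3%. A rounded 83% just misses: 120 × 0.83 = 99.6.

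**Step 5. Is the survival comparison affected?** No. 96 exceeds 66 by 30. Under the plan's own normal-means formula, 96 per group gives about 97% power.

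**Step 6. Is 125 feasible?** 25 × 5 = 125 surgical patients over the planned period. The corrected number equals the expected supply, with no margin for ineligibility or refusal.

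**The case against.** The arithmetic is hard to dispute; the case on the other side concerns its weight.

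- **The shortfall is small and spares the primary comparison.** This stands. Overall survival is the primary outcome, and its requirement of 66 per group is comfortably met. Because the basis for the 100 is not shown, nothing in the article demonstrates that a model built on 96 per group would be materially worse than one built on 100.
- **Patients lost to follow-up still count.** In Kaplan-Meier, log-rank and Cox analyses they contribute time until they are censored, so 96 is the number with complete follow-up rather than the number with any usable data. This is a fair qualification, but losses reduce the deaths observed, and the plan itself chose to enlarge the sample for them. Having made that choice, it should apply it correctly.
- **Recruitment may exceed 120 anyway.** The plan calls 120 a minimum, intends to enrol all nonsurgical patients over the five years, and expects about 125 surgical patients. The study could reach 125 per group without any redesign. The Abstract and Study Design nevertheless fix 240, and a floor that is miscalculated is still wrong.
- **Eligibility requires regular follow-up.** One inclusion criterion asks for follow-up beyond two years or to the endpoint, which might suggest little loss. The sample-size paragraph nonetheless assumes 80%, and its result has to agree with that.
- **The origin of 120 is inferred.** The article does not say that it was computed as 100 × 1.20. That is the only route found from the stated figures, but it remains an inference. The mismatch between 100, 80% and 120 does not depend on it.

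**Conclusion.** The point holds. At the assumed 80% follow-up, 120 enrolled per group gives 96 with complete follow-up and not 100: 4 short per group, 8 short in total, or 4% of the stated need. The enrolment consistent with the plan's own figures is 125 per group, 250 in total.

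The effect is confined to the prediction-model requirement. The conclusion rests on two readings of the text: that 100 is the number wanted after losses, and that 80% is the proportion of enrolled patients who complete follow-up. It does not depend on whether 100 was itself the right target. The error is modest, but it sits in the headline sample size and should be corrected.

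**What to change.** **Preferred: keep 120 and restate what it yields.** Replace the follow-up sentence with wording such as: *Enrolling 120 patients per group (240 in total) is expected to leave 96 per group (192 in total) with complete follow-up, assuming a follow-up rate of 80%.* The preceding statement that 100 per group are needed must change as well, with the prediction model sized on 192 (16 patients per factor for 12 factors) and the sizing method shown. Otherwise the contradiction merely becomes visible. This costs wording and a slightly less favourable figure, and no extra patients.

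**If 100 per group is firm.** Change the figures to 125 per group and 250 in total in the Abstract, Study Design, and Sample Size and Study Timeline. This adds 5 patients per group. The nonsurgical group should not be the constraint, since the plan says those patients are more numerous. The surgical group is: 125 is the whole of the expected five-year supply, so the plan should say what happens if some are ineligible or decline.

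**Weaker alternative.** Keep both 120 and 100 and state that follow-up of at least 83.3% (100 of 120) is required. This is defensible only if there is evidence that such a rate is achievable; otherwise it fits the assumption to the answer.

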### Patient Enrollment and Group Allocation

All patients with SMLC being treated at our center are potential candidates, and those who meet the inclusion and exclusion criteria will be eligible for enrollment in our study. Patients who receive surgical treatment along with postoperative systemic comprehensive treatment will be enrolled in the surgical group. Patients who receive only conservative treatment (eg, radiotherapy, chemotherapy, targeted molecular therapy, immunological therapy, etc) without surgical treatment will be enrolled in the nonsurgical group. All study procedures, as well as the participants’ rights, responsibilities, benefits, and risks, will be communicated, and participants will sign an informed consent form. Figure 1 displays the study flowchart.

In order to participate, patients will need to meet certain eligibility criteria. The inclusion criteria are (1) a pathological diagnosis of SMLC, (2) understanding and voluntarily participating in the study, and (3) being regularly followed up beyond 2 years or to the endpoint. Exclusion criteria include: (1) not receiving antitumor treatment at our hospital, (2) coexistence of spinal trauma or infection, (3) history of other malignancies, and (4) unwillingness to participate or inability to adhere to our follow-up schedule.

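### The target of 120 surgical patients in 5 years requires about 95% of everyone operated on to be enrolled, with no allowance for ineligibility or refusal

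*Protocol article*

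**What the plan says.** All the inputs are in the Methods of the protocol article.

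- **Rate and period** (Sample Size and Study Timeline): "There were approximately 25 patients undergoing surgery per year at our center; therefore, we plan to enroll the patients over the next 5 years".
- **Calendar window** (Study Design): enrolment runs "from June 1, 2022, to June 30, 2027", which is 61 months.
- **Target** (Sample Size and Study Timeline): 66 per group for the survival comparison. For the prediction model, "100 cases in each group are needed (the ratio of surgical to nonsurgical group is 1:1"). With an expected final follow-up rate of 80%, "a minimum of 120 patients will be required for each group".
- **Nonsurgical supply** (same section): nonsurgical patients are said to be the more numerous, and all those treated in the 5 years are to be enrolled.
- **Entry criteria** (Patient Enrollment and Group Allocation): the surgical group consists of operated patients who also have systemic treatment after surgery. Exclusions include "not receiving antitumor treatment at our hospital", coexisting spinal trauma or infection, another malignancy, and "unwillingness to participate or inability to adhere to our follow-up schedule". No proportion is attached to any of these.

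**The concern.** The 5-year period is derived from the number of patients operated on, while the target counts patients enrolled. The article itself separates the two: it treats every patient with the disease at the centre as a possible candidate and then applies the criteria. The 80% does not cover this step, because it describes follow-up after entry.

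Surgical patients are the scarce group, so their number limits the study. If an appreciable fraction of operated patients is ineligible or declines, the surgical group falls short of 120 and of the 100 evaluable that the model is said to need. The 1:1 ratio adds to the difficulty: read literally, it caps the group that could make up some of the lost precision.

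**Working it through.** **1. The plan's own figures.**

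- Survival comparison: n per group = (1.96 + 1.2816)² × (4² + 3²) / 2² = 10.508 × 25 / 4 = 65.7, so 66. This reproduces the stated 66 (two-sided 5%, 90% power, means 11 and 9 months, SDs 4 and 3).
- Period: 120 / 25 = 4.8 years, rounded to 5. This reproduces only if every operated patient is enrolled.
- Inflation: 100 × 1.2 = 120 reproduces the stated 120. To retain 100 at 80% follow-up the calculation is 100 / 0.8 = 125, since 120 × 0.8 = 96.

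**2. Capture needed.** Capture means the share of operated patients who are eligible, consent and enter the study.

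- Operated patients: 25 × 5 = 125, or 25 × 61/12 = 127.1 over the dated window.
- For 120 enrolled: 120/125 = 96.0%, or 120/127.1 = 94.4%.
- For 125 enrolled: 125/125 = 100%, or 125/127.1 = 98.4%.
- The rate is only approximate. At 24 per year, 120 needs 100% (98% over 61 months). At 26 per year it needs 92% (91%).

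**3. Size under assumed capture.** The documents give no fraction, so the first column is an assumption. Enrolled = 127.1 × capture; evaluable = enrolled × 0.8. The last two columns treat accrual as Poisson.

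| Assumed capture | Enrolled, 61 months | Evaluable | Chance of at least 120, 61 months | Same, 5.0 years |
|---|---|---|---|---|
| 100% | 127 | 102 | 75% | 69% |
| 90% | 114 | 92 | 31% | 25% |
| 80% | 102 | 81 | 4% | 3% |
| 70% | 89 | 71 | 0.1% | 0.1% |
| 60% | 76 | 61 | about 0 | about 0 |

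**4. Effect on the survival comparison.** To have 66 evaluable, 66 / 0.8 = 82.5 must be enrolled, and 82.5 / 127.1 = 65% capture. Above that, the plan's own requirement for this comparison is met.

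**5. Unequal groups.** At 60% capture there are 61 evaluable surgical patients. With the plan's means, SDs, alpha and power, solve 16/61 + 9/n = 4 / 10.508. This is 0.2623 + 9/n = 0.3807, so n = 9 / 0.1184 = 76.03, or 77 evaluable nonsurgical patients. At 80% follow-up that is 77 / 0.8 = 96.25, so 97 enrolled, which is fewer than the 120 already planned.

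**The case against.** **The rate alone reaches the target.** It gives 125 to 127, which is at least 120, and no criterion carries a proportion. A reader might infer that the plan's own figures show the surgical group will miss 120, or that 100 evaluable is out of reach at any realistic rate. The documents do not support that. A shortfall appears only once a capture fraction below about 95% is assumed, and even at 90% the chance of reaching 120 is 25% to 31%. This objection stands and limits the point to a missing allowance.

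**The 25 may already be screened.** The paragraph also draws on the centre's own retrospective study, so the figure could count eligible patients. The wording is patients undergoing surgery, and nothing says they were screened. The Treatment section also describes adjuvant SBRT and drugs as part of the centre's surgical workflow, so the requirement for postoperative treatment may remove few. One sentence from the sponsor would settle this.

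**The evaluable gap has two causes.** Even with 120 enrolled, only 96 are evaluable. That gap comes from inflating by 1.2 instead of dividing by 0.8, and it is not evidence of poor capture. It is therefore kept separate above.

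**Losses may overlap.** Ability to keep the follow-up schedule is an entry condition, so applying the full 80% afterwards may count some losses twice. Patients lost to follow-up also still contribute censored time to the Kaplan-Meier, log-rank and Cox analyses. Both points make the evaluable column somewhat pessimistic.

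**A shortfall need not stay hidden.** It might be thought that it would emerge only in year 5. Nothing says so: accrual can be counted each year, and Data Management and Supervision provides a team outside the study to monitor its progress.

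**Conclusion.** The point holds as a missing allowance. The stated 120 surgical patients can be enrolled in the planned period only at about 95% capture of everyone operated on (94% over 61 months, 96% over 5 years), if the 25 per year is unscreened, as its wording suggests. The margin over the whole period is 5 to 7 patients. Independently of any capture assumption, 100 evaluable at 80% follow-up takes 125 enrolled, which is the full 5-year volume.

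The consequence falls mainly on the prediction model: any capture below about 98% leaves fewer than 100 evaluable surgical patients by the plan's own reckoning. The 66 per group for the survival comparison is safe down to about 65%. The shortfalls in the table rest on assumed capture fractions, a constant rate of 25 per year and the stated 80% follow-up. The power figures carry over the plan's comparison of mean survival times, not a log-rank calculation.

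**What to change.** 1. Restate the expected surgical number as 25 per year × an eligible-and-consenting fraction × the enrolment period, taking the fraction from the centre's own series. If the 25 is already screened, say so.
2. Correct the inflation: 100 / 0.8 = 125 in place of 120, or state that 96 evaluable is accepted.
3. Remove the 1:1 ratio and the figure of 120 as a limit on the nonsurgical group. This agrees with the existing intention to enrol all nonsurgical patients.
4. Report the power of the survival comparison and the precision of the model at the resulting unequal numbers. For power, the plan's inputs give 90% with 61 surgical and about 77 nonsurgical evaluable patients. For the model, the sponsor should show that its sizing method accepts unequal groups; the article does not give enough to check this.

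The cost is a less favourable stated surgical group size and an unequal ratio. The change needs restated figures and a sentence on the expected ratio, with no extra surgical patients and no longer enrolment.
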